### Data management {19}

Household data, clinical measurements in cohort incidence study, and entomological data collected during the cross-sectional surveys will be captured on electronic forms using smartphones installed with ODK Collect. The data will be stored on a secure server located at LSHTM and all data management and manipulation will be done using Stata (Stata Corp). Laboratory data output will be available directly from the analyser (e.g. qPCR data) and imported into a database. Data extractions will be converted into Stata format for querying and analysis. It will be possible to share de-identified data in several widely used formats.

#### Data quality and control

Paper case report forms (CRFs) will have numbered and coded items to ensure straightforward and accurate data entry and processing, and drafts will be reviewed by the study team before finalisation. Standard Operating Procedures (SOPs) for data collection will be developed and field staff will be appropriately trained to ensure rigorous data collection. This will include quality control (QC) of their own performance by checking for missing data or implausible responses. Furthermore, more QC checks will be performed by a supervisor to check for data completeness and internal consistency of responses within a few hours of data collection. Corrections, when appropriate, will be done before the CRFs are submitted for data entry. Electronic CRFs will have built in checks for missing data, implausible responses, and internal consistency; data collected using electronic CRFs will include the device serial number and date/time stamp and the device will be password protected. All quantitative data collected on paper CRFs will be double-entered into a database independently by two data clerks. The database will maintain an audit trail with time-date stamps of data entry and all changes that are made to the data. Records of the username of the person who did the data entry and/or changed the record will be kept. A series of QC checks will be conducted during the initial review of the completed CRFs before data entry, during data entry, and during data validation. The checks which will be performed on all data will be specified in a detailed document (data checks document), which will be developed by the Data Manager and approved by the study team. This will include checks for range, values, and missing data. During the study, the data manager will prepare a regular QC report to document the current status of data entry and any corrective actions needed; this will be communicated to the field supervisors for resolution. In addition, before the database is locked, the data manager and team will perform a QC check of the database against the CRFs. This check will be based on a risk assessment and may, for example, include a 100% check of key variables, and a 10% check of the remainder of the database. After QC, and with agreement of the study team, the data manager will lock the database, withdrawing all write/edit permissions so that no further changes can be made.

#### Data security 

Every effort will be made to ensure data security, particularly relating to sensitive participant information. All data will be uploaded onto a secure server on the LSHTM cloud. All data will be stored encrypted and will be accessible only by password and encryption keys held by the data manager. In the study database, we will not store any information that could be used to identify individual study participants. We will use anonymised study numbers as our unique participant identifier.

The main risk to the confidentiality and security of information are names and housing coordinates acquired to link malaria prevalence results to geographical areas. This risk is managed by giving a unique identifier number to each participant and household. This confidential data is only managed by the project manager and will be kept separate from other databases in the short to medium term. It will then be stored securely and not on a shared drive so that anonymity is not lost in the long term.

#### Data storage 

Upon completion of the study, electronic files will be stored on a server and also copied to encrypted USB and stored offsite in a safebox. CRFs will be stored in the secure archive, which is equipped with locked cabinets for long-term storage of CRFs and documents. All paper source records will be retained for a minimum of 10 years from the point of publication of data on the primary outcome. Electronic data will be stored for a minimum of 10 years following study completion, with regular checks to make sure that the data are still readable.

### Confidentiality {27}

All procedures for data collection, management, storage, and manipulation will follow SOPs. To ensure confidentiality is maintained, paper CRFs with participants’ names will be stored in a locked cabinet and only accessible by authorised staff. This risk is also managed by giving a unique identifier number to each participant. All analyses will be done using the unique ID.

### Plans for collection, laboratory evaluation, and storage of biological specimens for genetic or molecular analysis in this trial/future use {33}

De-identified blood samples collected for filter paper blood spots and blood slides will be stored for 2 years at IPR and will be used for the current trial and potential future studies. Samples will be stored with a dessicant in a fridge at 4 to 8 °C). Samples will be identified using a QR code.

## Statistical methods

### Statistical methods for primary and secondary outcomes {20a}

Descriptive statistics (mean and standard deviation or median and interquartile range for continuous variables, and frequency and proportion for categorical variables) will be used to compare characteristics of participants between the study arms. All primary analyses will be conducted by intention to treat (ITT).

#### Primary outcome

The main analysis will be done on malaria case incidence collected over 12 months. Incidence of malaria cases in each dual AI LLIN treatment arm ( VEERALIN®LN and Interceptor® G2 LN) will be compared to the incidence of malaria cases in the reference arm (MAGNet® LN) to assess whether the new dual AI LLINs are superior to the reference LLINs. Children will be followed up for 12 months. Following any treatment for malaria, a child will not be considered at risk for 2 weeks and this period will be censored.

All analyses will be based on comparisons of incidence rates between clusters randomised to the three arms. Due to the relatively small number of clusters per arm (*n* = 11), analyses will take place at the cluster level. A summary measure will be obtained for each cluster and the arms will be compared using a two-sample *t*-test [34]. If the cluster-specific observations have a skewed distribution, they will be logarithmically transformed prior to the *t*-test.

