## Assignment of interventions: allocation

### Sequence generation {16a}

Restricted randomisation will be used to allocate the 33 clusters into the three study arms. Important variables will be balanced between the three study arms (baseline malaria infection prevalence in children aged 0.5 to 10 years, cluster-level LLIN usage (prior to distribution), socio-economic status and village size). The randomisation method will allow us to limit the difference of these selected variables between the arms. At least 10,000 sequences will be generated and one will be randomly picked using a random number generator.

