#### Secondary outcomes

Prevalence of malaria infection in the study clusters will be estimated at baseline and 6 and 12 months. Prevalence will be measured in all age groups in the study clusters. As for the incidence outcome, due to the relatively small number of clusters, analyses will primarily take place at the cluster level, with cluster-level proportions compared using a *t*-test. Depending on the distribution of proportions at the cluster level, a logarithmic transformation may be used before the *t*-test. The primary comparison will be 12 months post net distribution.

The level of antibodies to mosquito salivary peptides will be measured in samples taken at baseline and 6 and 12 months after net distribution in the same population randomly selected to take part in the infection prevalence survey. Serological outcomes will be expressed in proportion positives with the threshold for positivity defined using a mixture model.

EIR will be estimated as *Anopheles* density collected in the HLCs per house per night multiplied by the proportion of sporozoite-infected vectors*.* Cluster-level results will be compared using a *t*-test, using a logarithmic transformation if necessary.

Adverse events (AEs) and serious adverse events (SAEs), their severity and relation to the intervention will be examined and tabulated by study arms.

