### Methods for additional analyses (e.g. subgroup analyses) {20b}

The impact of covariates such as baseline prevalence age of child, gender, socio-economic status, distance to health facility, etc. on malaria incidence will be analysed, where regression is carried out on the individual-level data (ignoring the clusters) and then comparing the residuals for each cluster based on the observed outcome, compared to the predicted outcome, in the absence of an intervention effect. Comparison of the residuals using a *t*-test will provide a measure of intervention effect, adjusted for covariates.

For malaria infection prevalence data, subgroup analysis will include investigating individual level, household level, distance to health facility, and cluster-level characteristics, such as age group, socio-economic status, household construction, vector species composition, cluster net coverage, and insecticide resistance intensity. These analyses will be performed on the residuals of the cluster-level results, as documented for the incidence analyses. Secondary analyses with EIR data will include adjusting for timepoint and comparing residuals of the cluster-level summaries.

Where possible, geospatial models of vector species distribution and insecticide resistance across the study area will be developed using machine learning algorithms incorporating entomological field indices linked to the point locations of vector sampling alongside earth observation data on relevant covariates (e.g. climate, vegetation indices, elevation, land cover/land use, population density).

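### Allocation is restricted on four cluster variables but the primary test adjusts for none of them, so precision is given up to the extent that those variables are prognostic

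*Protocol article*

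**What the plan says.** Sequence generation {16a} states: "Restricted randomisation will be used to allocate the 33 clusters into the three study arms". The variables are "baseline malaria infection prevalence in children aged 0.5 to 10 years, cluster-level LLIN usage (prior to distribution), socio-economic status and village size", and the stated purpose is that "The randomisation method will allow us to limit the difference of these selected variables between the arms". No numerical limit is given for how close the arms must be.

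Under Statistical methods {20a}, Primary outcome, the small number of clusters (11 per arm) is the reason given that "analyses will take place at the cluster level". The test follows: "A summary measure will be obtained for each cluster and the arms will be compared using a two-sample" t-test, on the log scale if the cluster values are skewed. No covariate enters and nothing reflects the restriction.

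Infection prevalence is handled in the same way under Secondary outcomes: "Depending on the distribution of proportions at the cluster level, a logarithmic transformation may be used before the" t-test, with the 12-month survey as the main comparison.

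Adjustment appears under Methods for additional analyses {20b}: "The impact of covariates such as baseline prevalence age of child, gender, socio-economic status, distance to health facility", and others left open, is to be examined by an individual-level regression whose cluster residuals are then compared by t-test.

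**The concern.** Restriction discards allocations in which the arms differ much on the chosen variables. If those variables predict incidence, the arm difference varies less over the allocations that could have been drawn than it would under free randomisation. A two-sample t-test takes its standard error from the spread between clusters within arms. That spread still contains the part explained by the restriction variables, so the standard error is too large, the test rejects a true null less often than its nominal level, and the interval is wider than the design warrants. A cluster-level model with the same variables removes the explained part from the residual.

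At stake is interval width in a trial with 11 clusters per arm. The Sample size section already allows for a PBO effect below that of an earlier trial, and precision matters most if the true effect is smaller still.

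**Working it through.** **Inputs.** From Sample size {14}: 1.2 v 0.78 episodes per child-year, between-cluster coefficient of variation k = 0.29, 45 evaluable children per cluster for 12 months, 11 clusters per arm, 80% power. Assumed: two-sided alpha of 0.05, the prognostic strength of the restriction variables, and the tightness of the restriction.

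**1. The plan's own figure.** Hayes–Bennett for rates:

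c = 1 + (1.960 + 0.842)² × [(λ0 + λ1)/y + k²(λ0² + λ1²)] / (λ0 − λ1)²

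= 1 + 7.849 × [1.98/45 + 0.0841 × 2.0484] / 0.42² = 1 + 7.849 × 0.2163/0.1764 = 10.62, so 11.

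The stated 11 per arm reproduces. Power at 11 is 81.5% by this formula and 81.3% by noncentral t on 20 df. The formula has no term for restriction or covariates.

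**2. Why cluster-level predictors can matter.** The between-cluster share of the variance of a cluster rate is k²λ²/(k²λ² + λ/45):
- reference arm: 0.1211/(0.1211 + 0.0267) = 82%
- intervention arm: 0.0512/(0.0512 + 0.0173) = 75%

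**3. Direction.** Simulation of 33 clusters with log cluster rates and Poisson counts over 45 child-years. Four error-free covariates explain a share R² of the between-cluster variance (prevalence carries 70% of it). Allocation is restricted to a largest arm difference below 0.5 SD on each. 4,000 runs; the first three columns are under no effect.

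| R² | true SD of log rate difference | mean t-test SE | type I error, restricted | type I error, unrestricted |
|---|---|---|---|---|
| 0 | 0.139 | 0.135 | 5.0% | 5.7% |
| 0.25 | 0.127 | 0.135 | 4.1% | 5.4% |
| 0.5 | 0.120 | 0.136 | 2.5% | 4.8% |
| 0.7 | 0.109 | 0.138 | 1.4% | 5.2% |

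For R² of 0.25, 0.5 and 0.7 the SE is too large by 0.135/0.127 = 6%, 0.136/0.120 = 13% and 0.138/0.109 = 27%. Without restriction there is no such pattern, so the conservatism comes from the restriction combined with an unadjusted test.

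**4. Measurement error.** Baseline prevalence comes from a survey of 50 people of all ages per cluster. At prevalence 50% and k = 0.29, the between-cluster variance is (0.145)² = 0.0210, and the sampling variance is (0.25 − 0.0210)/n. The protocol gives no age distribution. If about 15 of the 50 are aged 0.5 to 10 years (an assumption), reliability is 0.0210/(0.0210 + 0.0153) = 0.58. With all 50 it would be 0.0210/(0.0210 + 0.0046) = 0.82. A value of 0.6 is used below.

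**5. Size with that error.** Restriction on four variables; r is the correlation of baseline prevalence with log incidence between clusters. The adjusted analyses are one linear model on all 33 clusters, with 33 − 3 − 1 = 29 or 33 − 3 − 4 = 26 residual df, against 20 for the t-test. Power is at a rate ratio of 0.65.

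| r | type I error, unadjusted | power, unadjusted | power, prevalence-adjusted | power, all four |
|---|---|---|---|---|
| 0.3 | 4.5% | 83% | 86% | 84% |
| 0.5 | 3.8% | 84% | 89% | 87% |
| 0.7 | 3.0% | 85% | 91% | 90% |

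The gain from adjusting for prevalence is 3, 5 and 6 points; from all four it is 1, 3 and 5. At r = 0, prevalence alone costs nothing and all four cost 1 to 2 points. With 4,000 runs the Monte Carlo SE of a 5% rate is √(0.05 × 0.95/4000) = 0.3 points, so the type I error at r = 0.3 is hardly distinguishable from nominal.

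**The case against.** The unadjusted cluster-level t-test is a legitimate and deliberate choice. It is justified in the text by the number of clusters and agrees with the sample-size method. It does not inflate type I error, and in every scenario its power stays above the planned 80%. All of this stands. A reader might infer that the trial is underpowered or its primary test invalid; the figures support neither.

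A reader might also take it as established that the intervals are too wide. The documents do not show that, because they give no correlation and no restriction limit. Eligibility {10} also admits only villages with estimated prevalence above 50%, which may narrow the covariate's range and weaken it further. Much larger gains appear only with a strong predictor measured without error: for one such covariate at r = 0.7, simulated power is 89% unadjusted and 97% adjusted. A village prevalence from a small sample does not meet that condition.

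Nor is adjustment absent. Section {20b} already plans it, and its covariate list is open-ended, so not naming net usage and village size there is no fault. What remains in dispute is which analysis is primary.

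Lastly, a separate t-test for each pair of arms is not wrong. Pooling all three arms assumes a common variance. On the raw scale with constant k that would fail (0.29 × 1.2 = 0.35 v 0.29 × 0.78 = 0.23); on the log scale it is reasonable.

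These points reduce the size and the certainty. They do not remove the mismatch between how villages are allocated and how the arms are compared.

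**Conclusion.** The point holds as a matter of efficiency. Allocation uses four cluster variables that the protocol itself calls important, and the primary test uses none. To the extent that they are prognostic, the standard error is too large and precision is given up. Under the plan's figures, two-sided alpha of 0.05 and baseline prevalence with reliability 0.6, the power forgone against a prevalence-adjusted model is about 3 to 6 points for a correlation of 0.3 to 0.7. It is more if prevalence were error-free and none if the correlation is zero. The direction is secure; the size depends on quantities that the protocol does not state. The change is worth making because the downside is small, but the trial's validity does not depend on it.

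**What to change.** Make a covariate-adjusted cluster-level analysis primary. One suitable form is a linear model of log cluster incidence on arm, fitted to all 33 clusters, with the two contrasts against the reference arm. Adjust at minimum for the same baseline prevalence variable that is used in the restriction. Adding the other three restriction variables is acceptable. Fix the covariates before outcome data are seen.

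Promoting the residual method of {20b} would also serve, provided that the restriction variables are named and the degrees of freedom are reduced for cluster-level covariates.

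Keep the unadjusted t-test as a supportive analysis. Adjust the 12-month prevalence comparison for baseline prevalence in the same way; its gain was not quantified here.

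The cost is wording only, since the restriction variables have to be available for the randomisation. The statistical price is a few residual degrees of freedom, about 1 to 2 points of power if all four variables are included and predict nothing, and the assumption of a common variance on the log scale.

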#### Secondary outcomes

Prevalence of malaria infection in the study clusters will be estimated at baseline and 6 and 12 months. Prevalence will be measured in all age groups in the study clusters. As for the incidence outcome, due to the relatively small number of clusters, analyses will primarily take place at the cluster level, with cluster-level proportions compared using a *t*-test. Depending on the distribution of proportions at the cluster level, a logarithmic transformation may be used before the *t*-test. The primary comparison will be 12 months post net distribution.

The level of antibodies to mosquito salivary peptides will be measured in samples taken at baseline and 6 and 12 months after net distribution in the same population randomly selected to take part in the infection prevalence survey. Serological outcomes will be expressed in proportion positives with the threshold for positivity defined using a mixture model.

EIR will be estimated as *Anopheles* density collected in the HLCs per house per night multiplied by the proportion of sporozoite-infected vectors*.* Cluster-level results will be compared using a *t*-test, using a logarithmic transformation if necessary.

Adverse events (AEs) and serious adverse events (SAEs), their severity and relation to the intervention will be examined and tabulated by study arms.

For whole transcriptomic sequencing, total RNA will be isolated from pools of 5–10 *An. gambiae* s.s., *An. coluzzii*, or *An. funestus* s.s., per phenotypic group (i.e. “resistant”—survived exposure to five or ten times the discriminating insecticide concentration; or “unexposed”—mosquitoes from the same field population, which were not exposed to insecticide in control bioassays) and used to prepare RNA-seq libraries for next-generation sequencing, following ribosomal RNA depletion. To obtain sufficient sequencing coverage and depth, our previous RNA-seq experiments have typically comprised nine libraries (two wild populations in technical triplicate and one susceptible colony comparator, also in triplicate—either *An. gambiae* s.s. Kisumu, *An. coluzzii* N’Gousso, or *An. funestus* s.s. FANG), sequenced at 2 × 125 bp paired-end reads on an Illumina Hi-Seq platform [18]. Following sequencing read alignment to annotated reference transcriptome assemblies, available from VectorBase [43] differentially expressed genes (DEGs) will be identified using the standardised DESeq2 pipeline [44]. To account for induction of gene expression during insecticide bioassays, pairwise comparisons of DEGs between “unexposed” field mosquitoes and “susceptible” colony mosquitoes will allow for the identification of significantly over- or under-expressed RNA transcripts, which are associated with constitutive resistance, while comparisons between “resistant” field mosquitoes and “unexposed” field mosquitoes will detect changes in gene expression in response to chemical exposure. Candidate genes, implicated in particular resistance profiles, will be validated by real-time quantitative PCR (RT-qPCR) and developed into multiplex TaqMan RT-qPCR assays to use for surveillance of insecticide resistance selection and changes in relative intervention performance in the cRCT [45].

For whole genome sequencing, total DNA will be isolated from individual *An. gambiae* s.s., *An. coluzzii*, or *An. funestus* s.s., per phenotypic group (i.e. “susceptible”—died following exposure to the discriminating insecticide concentration; or “resistant”—survived exposure to five or ten times the discriminating insecticide concentration) and used to prepare multiplex libraries for sequencing at 2 × 150 bp paired-end reads on an Illumina Hi-Seq platform. Sequence reads will be aligned to the appropriate species reference genome (*An. gambiae* s.s.: AgamP3; *An. coluzzii*: AcolN1.1; or *An. funestus* s.s. AfunF3) from VectorBase [43], using bwa-0.7.9-r783, sorted using samtools 0.1.17, and potential genetic variants (including single-nucleotide polymorphisms and insertion/deletions) will be identified using the Genome Analysis Toolkit (GATK) v4.2.2.0. and copy-number variants (CNVs) and structural re-arrangements will be screened for using Hidden Markov Models (HMMs) [46]. Genetic variants will be developed into novel, custom insecticide- or intervention-specific amplicon-sequencing panels for surveillance in the cRCT [47].

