The proposed study area is characterised by much higher malaria transmission intensity and more intense pyrethroid resistance in local vectors compared to previous cRCTs done in East and West Africa. For example, the entomological inoculation rate (EIR) ranged between 0.35 and 2.20 per night in several districts in central Côte d’Ivoire [18] compared to an EIR of 0.28 in Benin [19] and 0.15 in Tanzania [20]. It is, therefore, vital to demonstrate that these next-generation LLINs, which are becoming the standard of care in SSA, are superior to standard py-LLIN in the most extreme resistance areas, as this is likely where alternative interventions will be most needed to sustain gains in malaria control. This trial will generate the first epidemiological evidence on the efficacy of PBO-py LLINs compared to py-LLINs in West Africa. This protocol is reported in accordance with the Standard Protocol Items: Recommendations for Interventional Trials (SPIRIT) 2013 Statement [21].

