**Fig. 1 Fig1:**
[figure not shown]
Map of Tiebissou department, central Côte d’Ivoire. Source of map: own from the study investigators ([name])

There is one main malaria season from May to November. The Lacs district is characterised by intense indoor malaria transmission with a prevalence of malaria reaching 51.3% in children under 5 years old, according to the DHS conducted in 2021 [15]. Net usage for the same period and age group in the Lacs district was 55.3%.

Recent data in a neighboring district showed extremely high resistance intensity (> 1500-fold) to the pyrethroid deltamethrin in *An. gambiae* s.s. and *An. coluzzii*, and < 30% mortality after exposure to py-LLIN. The 1014F kdr mutation was almost fixed (≥ 90%). The carbamate and organophosphate resistance‐associated Ace-1 G119S mutation was also detected at moderate frequencies (22–43%). Transcriptomic analysis identified overexpression of P450 genes (i.e. Cyp6P3 expression up to 33-fold) [17, 23]. Data collected in 2021 by VectorLink demonstrated susceptibility of local vectors to chlorfenapyr in the Gbeke region [24].

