### Eligibility criteria {10}

Thirty-three clusters will be included in this study based on the following criteria: being within a 2-h drive from Tiebissou town and at least 2 km away from other included clusters (in order to avoid cross-contamination), an estimated malaria prevalence of over 50% during baseline survey, and the acceptance of the hamlet leader and population.

The cohort will enroll randomly selected children (aged 6 months to 9 years old) who are resident in study villages and whose parents/caregivers have given written informed consent for their child to be included in the study. Children who are expected to be non-resident over the period of study will be excluded.

During cross-sectional malaria prevalence surveys, a maximum of 2 randomly selected household members who have resided in the village over the preceding 3 months, and who provide written informed consent for adults and parental/caregiver consent (and assent for children above 10) for children will be included. Vacant or unfound dwellings, severely ill inhabitants, and the absence of an adult capable of consenting will be reasons for exclusion.

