**Entomological outcomes**			
Indoor and outdoor Anopheles density	Human landing catch (HLC)	Entomology surveillance	6 houses per cluster every 2 months in all clusters for 12 months
Mosquito sporozoite rate	qPCR would serve to estimate the EIR [31]	Entomology surveillance	Subsample (30%) of the mosquito collected in HLC
Anopheles species identification	*An. gambiae, An.coluzzii* and *An. funestus* using Taq Man real-time PCR [32]	Entomology surveillance	Subsample of mosquitoes collected
Phenotypic resistance	WHO cylinder/CDC bottle assays [33]	Collection of larvae and/or adult *Anopheles* resting indoor	At baseline and at the end of the first year in 3 clusters per arm
Identification of molecular and metabolic insecticide resistance mechanisms	Screening for metabolic enzyme over-expression by RNA-seq Screening for resistance-associated mutations and copy-number variants by whole genome sequencing	Unfed 3-day-old adult *Anopheles* from larval collections phenotyped in bioassays	At baseline and at the end of the first year in 3 clusters per arm
Population-level genotypic resistance	Monitoring changes in key enzyme expression (identified by RNA-seq) using qRT-PCR Monitoring changes in frequencies of key mutations (identified by whole genome sequencing) using amplicon-seq	Unfed 3-day-old adult *Anopheles* from larval collections phenotyped in bioassays	At baseline and at the end of the first year in 3 clusters per arm
Serological responses to mosquito salivary peptides	Blood spots on filter paper will be utilised to measure the level of antibodies in residents blood as a proxy for exposure to mosquito bites	Cross-sectional survey	Baseline, 6 and 12 months post net distribution

*qRT-PCR* quantitative real-time polymerase chain reaction, *WHO* World Health Organization, *CDC* Center for Disease Control

The primary outcome measure will be incidence of malaria cases in children aged 6 months to 10 years over 1 year. A malaria case is defined as a fever above 37.5 °C or history of a fever in the last 48 h and a positive RDT. Malaria cases will be recorded at visits to cohort children, which will take place every 2 weeks during the malaria transmission season and every 4 weeks during the dry season.

Secondary outcomes include:Malaria infection prevalence (by RDT) in the study population of all ages at 6 and 12 months post net distribution.Vector density and EIR as a proxy for malaria transmission rate in the primary vector species.

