Other outcomes are:Serological responses to mosquito salivary antigens as a proxy for exposure to bites: this will be measured by detecting antibodies to salivary peptide gSG6-P1 using enzyme-linked immunosorbent assay (ELISA)At baseline and 12 months post-net distribution: phenotypic resistance to alpha-cypermethrin, PBO + alpha-cypermethrin and chlorfenapyr will be assessed using WHO cylinder and CDC bottle bioassays. In addition, CDC resistance intensity tests with alpha-cypermethrin alone (5, 10, 15 × the diagnostic dose; DD) and following PBO pre-exposure will be performed.At baseline, we will identify mechanisms of insecticide resistance in the main vector populations using Illumina whole-genome sequencing and RNA-seq and develop trial site-specific panels of resistance markers for post-intervention monitoring. During the trial, selection for resistance will be monitored by measuring changes in levels of metabolic enzyme expression (using qRT-PCR) and frequencies of resistance-associated mutations and copy-number variants (using amplicon-sequencing), at 12 months post-intervention between study arms.Net quality: Bio-efficacy testing and chemical content of nets will be assessed after they arrive in Côte d’Ivoire and at 12 months post-intervention.

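### The gSG6-P1 antibody level, measured as a proxy for bite exposure, is cut to a proportion positive; the log level by cluster would keep more information and would not depend on where a mixture-model threshold falls

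*Protocol article*

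**What the plan says.** Three places in the protocol article bear on this.

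- **What is measured.** Table 1 says that filter-paper blood spots will be used to "measure the level of antibodies in residents blood as a proxy for exposure to mosquito bites". The statistical section on secondary outcomes agrees: "The level of antibodies to mosquito salivary peptides will be measured in samples taken at baseline and 6 and 12 months after net distribution".
- **How it is analysed.** The same section then fixes the scale: "Serological outcomes will be expressed in proportion positives with the threshold for positivity defined using a mixture model". It states no analysis of the level itself. It does not give the number of mixture components or the rule that turns the fitted mixture into a cut-off.
- **How it ranks.** Outcomes {12} lists "Serological responses to mosquito salivary antigens as a proxy for exposure to bites" under other outcomes (gSG6-P1 by ELISA). It is not in the list of secondary outcomes, although its method appears under that heading in the statistical section.

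On the setting, the background reports that "the entomological inoculation rate (EIR) ranged between 0.35 and 2.20 per night in several districts in central Côte d’Ivoire". The study setting section adds: "The Lacs district is characterised by intense indoor malaria transmission". The eligibility criteria require "an estimated malaria prevalence of over 50% during baseline survey" for a cluster to enter.

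**The concern.** The antibody level is meant to show how much residents are bitten. Nets can lower biting without abolishing it, so the plausible effect is a downward shift in level among people who remain exposed. A yes/no cut registers only the people whom that shift carries across the threshold.

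A mixture-model threshold also relies on two distributions that can be told apart. Where transmission is intense, a distinct low-exposure group may be too small to anchor the lower component, and the threshold may then settle at an arbitrary point among exposed people.

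The same statistical section keeps the other exposure measure, the entomological inoculation rate (EIR), quantitative and allows a log transformation. The antibody level is treated differently without a stated reason.

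At stake is how the serology is read. Human landing catches count mosquitoes landing on volunteers in six houses per cluster, on one night every two months. Serology reflects bites received by residents living with the nets. A null result produced by the cut-off could be misread as no reduction in their exposure.

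**Working it through.** **1. The plan's own figure for this survey sample.** No power is stated for serology. The people tested are those of the prevalence survey: m = 50 per cluster, c = 11 clusters per arm, 50% versus 32.5% prevalence, between-cluster coefficient of variation k = 0.29, 80% power stated. Taking two-sided alpha 0.05 (assumed):

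- variance of the difference = {[p0(1−p0) + p1(1−p1)]/m + k²(p0² + p1²)}/(c−1) = {0.4694/50 + 0.0841 × 0.3556}/10 = 0.00393, so SE = 0.0627
- power = Φ(0.175/0.0627 − 1.96) = 0.797

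The stated 80% reproduces, so m = 50 and c = 11 are sound design inputs.

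**2. Exposure.** 0.35 × 365 = 128 and 2.20 × 365 = 803 infective bites per unprotected person-year. Total bites are more numerous than infective ones. This makes a sizeable unbitten group unlikely but does not measure one.

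**3. Where a mixture threshold might fall.** Surveys of 33 × 50 = 1650 people were simulated with assumed log levels: exposed N(0, 1), unexposed N(−2.5, SD 0.6). A two-component Gaussian mixture was fitted to each.

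- With 0 to 5% unexposed, the lower component took a median 44 to 49% of the sample, so it split exposed people instead of isolating the unexposed.
- The median positive share was then 2 to 7% with a cut at the lower mean + 2 SD, and under 1% at + 3 SD. Classifying by posterior probability above 0.5 gave roughly half to three quarters positive.
- With 10% unexposed, the + 2 SD rule gave positive shares from 2% to 68% across runs (5th to 95th percentile).
- With 30 to 50% unexposed, the split was well identified.

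So the result depends on a distribution and a rule that the protocol does not give.

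**4. Information lost by cutting.** Let p be the positive share, z its normal quantile and φ the normal density. For a small shift in a normal log level, the information kept per person is φ(z)²/[p(1−p)].

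The planned analysis is at cluster level, so between-cluster variance must be included. With total variance 1 and ICC ρ:

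- continuous cluster mean: Vc = ρ + (1−ρ)/50
- binary cluster proportion: Vb = Var(p_j) + E[p_j(1−p_j)]/50, with p_j = Φ((z+u)/√(1−ρ)) and u ~ N(0, ρ)
- share kept: E = φ(z)² Vc/Vb
- power, where the continuous analysis has 80%: Φ(√E × 2.802 − 1.96)

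Example with p = 0.90 and ρ = 0.02: Vc = 0.0396, Vb = 0.00241, φ = 0.1755. E = 0.0308 × 0.0396/0.00241 ≈ 0.51, and power ≈ 0.51.

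| Positive share | Kept per person | Kept at cluster level, ICC 0.02 to 0.20 | Power, ICC 0.02 to 0.20 |
|---|---|---|---|
| 50% | 64% | 78–94% | 0.69–0.78 |
| 80% or 20% | 49% | 65–86% | 0.62–0.74 |
| 90% or 10% | 34% | 51–75% | 0.51–0.68 |
| 95% or 5% | 22% | 36–63% | 0.39–0.60 |

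The formulas are symmetric in p and 1−p, so a very low positive share costs as much as a very high one.

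**The case against.** A reader might infer that nearly everyone will test positive, that the mixture has no unexposed group to find, and that most of the exposure signal is therefore lost. The protocol does not support that reading.

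- It gives no antibody distribution, seroprevalence or cut-off rule. In step 3, with few unexposed people, the typical positive share lay near the floor or in the middle, not at a ceiling.
- A mixture needs separable low and high distributions, not strictly unbitten people. A split of low from high responders could still be usable, with a different meaning.
- The quoted EIR comes from several districts, not the trial villages. If it rests on landing catches, as the trial's own EIR will, it describes exposed catchers and not residents under nets. Earlier net use in under-fives in the Lacs district was 55.3%, and the trial aims for 75% usage.
- The per-person losses overstate the cost for a cluster-level comparison. With a cut near the median, the cluster-level loss is only about 6 to 22%.
- Serology is an other outcome and plays no part in the sample size. Biting is measured directly by landing catches in every cluster, with vector density and EIR as listed secondary outcomes.

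All of this stands, and it limits the size and certainty of the point. A last argument is that a continuous analysis could be left to the statistical analysis plan. That is weaker: the article does not leave the scale open but states a binary one. Nothing in it forbids analysing the level as well, so the change is easy to make.

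**Conclusion.** The point holds as an inexpensive improvement to an other outcome. The plan fixes a dichotomised scale for a measure that is continuous by design. Some loss is certain under the normal model, since no cut keeps more than 64% of the per-person information. For the planned cluster-level comparison, 80% power on the continuous scale becomes about 0.69 to 0.78 at 50% positive and 0.51 to 0.68 at 90% or 10% positive. Where the cut-off will fall is unknown, and it may be unstable if the low-exposure group is small.

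These figures assume normal log levels, a small shift of equal size for everyone, 50 samples per cluster and an ICC of 0.02 to 0.20. The protocol supplies only the 50. The primary outcome, infection prevalence, vector density and EIR are unaffected.

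**What to change.** In the statistical section, make the cluster mean of log gSG6-P1 level (the geometric mean) at 6 and 12 months the main serological comparison. Compare each dual-ingredient arm with the reference arm by the cluster-level t-test already planned for the other outcomes.

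Keep proportion positive as a supportive summary. Fix one threshold from the pooled baseline data of all arms and apply it unchanged to every arm and to both later surveys, so that a shift in the distribution cannot move its own cut-off.

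The cost is wording. The planned ELISA already yields the continuous value, and no further samples or visits are needed. The small downside is that a geometric mean level is less familiar to readers than a seroprevalence.
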